##### Endpoints

The primary trial endpoint will be a change in Hb concentration, measured by HemoCue®, on the day of inclusion, and post‐intervention at the end of malaria transmission season, that is, 1 month after the last SMC cycle. The secondary endpoints will include incidence of clinical malaria, defined as fever of >37.5°C or a history of fever in the preceding 48 h, and a positive malaria blood film of any parasite density, detected by passive case detection during the surveillance period; change in prevalence of anaemia between the day of inclusion and post‐intervention at the end of malaria transmission season (anaemia will be defined as an Hb less than 11 g/dL); the incidence of solicited adverse events and adverse drug reactions assessed to be related to the study medications during a period of six consecutive days after administration of study drugs; prevalence and density of *Plasmodium falciparum* infection at the post‐intervention survey; prevalence and density of helminth infection; and prevalence and density of malaria‐helminth co‐infection at the post‐intervention survey. Tertiary endpoints will include the cost per child treated per year and the cost per anaemia case averted calculated by a cost analysis, and the incidence of anaemia among the children in the intervention and control arms will be used to estimate the incremental cost‐effectiveness of integrated SMC plus anthelminthic treatment versus SMC alone, in terms of incremental economic costs per DALY averted (Box 1).

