### Statistical analysis plan

The field and laboratory data will be merged, harmonised, cleaned and analysed with STATA® version 18.1 SE (Stata Corp., College Station, TX, USA). Descriptive statistics such as frequencies and proportions will be used to summarise the baseline parasitic parameters and socio‐demographical characteristics of the study participants by cluster arm. Data will be analysed using an ITT approach. The proportions of adverse events and the incidence (average number per participant) of reported adverse events will be compared between the study groups using the Chi‐squared test. Logistic regressions with robust standard errors will be used to estimate odds ratios and 95% confidence intervals. Wald tests will be used to assess the evidence of difference in odds between study groups, after controlling for baseline characteristics (sex, age group, weight and malaria and helminth infections' occurrence). Effect modification between intervention period and study groups will also be investigated using the Wald test. The geometric means of the *P. falciparum*, STH and schistosome intensities will be estimated and plotted before and after intervention periods. A univariable Poisson regression with robust standard error and Wald test will be used to compare the pre‐intervention parasites intensities across groups, and a multivariable Poisson regression including the pre‐intervention parasites intensities as a covariate, adjusting for other baseline characteristics described above, and Wald test will be used to compare the post‐intervention parasites intensities. The proportions of adverse events and the incidence (average number per participant) of reported adverse events will be compared between the study groups using the Chi‐squared test. All statistical tests will be two‐sided at a significance of *α* <0.05.

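### The logistic model's stated covariates omit baseline Hb and baseline anaemia, although the anaemia endpoint is a change from inclusion; if both surveys share one model, the period-by-group term is the treatment effect

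*Protocol article*

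**What the plan says.** Under Endpoints, the article lists as secondary the "change in prevalence of anaemia between the day of inclusion and post‐intervention at the end of malaria transmission season", and "anaemia will be defined as an Hb less than 11 g/dL". The primary endpoint in the same section is the change in Hb itself, so Hb at inclusion is available for the trial children.

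Under Statistical analysis plan:

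- Model: "Logistic regressions with robust standard errors will be used to estimate odds ratios and 95% confidence intervals".
- Test: "Wald tests will be used to assess the evidence of difference in odds between study groups".
- Adjustment: "after controlling for baseline characteristics (sex, age group, weight and malaria and helminth infections' occurrence". Neither Hb nor anaemia at baseline is in this list.
- Further test: "Effect modification between intervention period and study groups will also be investigated using the Wald test".
- For parasite intensities after treatment, by contrast, a "multivariable Poisson regression including the pre‐intervention parasites intensities as a covariate" is planned.

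The section does not name the outcomes of the logistic model, nor say whether it takes post-intervention records alone or both surveys.

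**The concern.** An endpoint worded as a change from inclusion invites an analysis that uses the inclusion value. The plan does this for parasite intensities but not for anaemia, although the baseline measurement is already collected. Baseline Hb is likely to be among the strongest predictors of endline anaemia, and with only 20 randomised communities a chance difference in baseline anaemia between arms is quite possible. Leaving it out costs precision and leaves such an imbalance uncorrected.

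The second matter is conditional. A period-by-group term can be fitted only when both surveys are in the model. Treatment starts on Day 0, after the baseline measurement. In a two-survey model without the interaction, the group coefficient therefore averages a period before any study drug with the period after it. The interaction is then the treatment effect, and calling it effect modification would mislabel it.

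**Working it through.** **Inputs from the article.** Control mean Hb 10.5 g/dL, intervention mean 11.0 g/dL, SD 1.5 g/dL, intra-class correlation 0.05, 10 communities of 60 children per arm (Sample size determination); anaemia cut-off 11 g/dL (Endpoints); two-sided 5% level (Statistical analysis plan).

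**Assumptions not in the article.** Both arms have mean Hb 10.5 g/dL at baseline and the control mean does not move. Baseline-to-endline correlation of Hb is 0.3 to 0.7 within child and 0.3 to 0.9 between communities. No other covariates are modelled.

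**1. The plan's own power figure.** Design effect = 1 + (60 − 1) × 0.05 = 3.95. Effective size per arm = 600 / 3.95 = 151.9. Standard error = 1.5 × √(2 / 151.9) = 0.172. Standardised difference = 0.5 / 0.172 = 2.91. Power is 82.8% by the normal approximation and 78.4% by the noncentral t with 18 df. The stated 80% lies between the two, so the inputs are sound to build on.

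**2. Implied anaemia effect at endline.** Control: Φ((11 − 10.5) / 1.5) = Φ(0.333) = 63.1%. Intervention: Φ(0) = 50%. Odds ratio = (0.50 / 0.50) / (0.631 / 0.369) = 0.586; the simulated average is about 0.58.

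**3. Period-averaged group term.** With no difference at baseline, the log odds ratio is roughly halved: exp(½ × ln 0.58) = √0.58 = 0.76.

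**4. Power by simulation.** 400 trials per row, logistic regression with community-robust standard errors, t with 18 df:

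| Correlation, child / community | Endline only | Endline + baseline anaemia | Endline + baseline Hb | Period by group | Group term, both surveys |
|---|---|---|---|---|---|
| 0.3 / 0.3 | 76.7% | 79.2% | 81.2% | 58.5% | 39.0% |
| 0.5 / 0.5 | 74.0% | 84.8% | 86.3% | 68.0% | 35.0% |
| 0.5 / 0.8 | 75.5% | 89.7% | 95.5% | 89.0% | 31.0% |
| 0.7 / 0.7 | 75.2% | 92.2% | 94.8% | 85.5% | 30.7% |
| 0.7 / 0.9 | 73.8% | 98.0% | 99.8% | 98.0% | 28.7% |

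Mean odds ratios: about 0.58 for endline only and for period by group; about 0.76 for the group term over both surveys; 0.49–0.57 adjusted for baseline anaemia; 0.44–0.56 adjusted for baseline Hb. The adjusted values lie further from 1 because they are conditional odds ratios, not because the effect is larger. Monte Carlo error near 75% is √(0.75 × 0.25 / 400) = 2.2 points, which accounts for the drift in the endline-only column.

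A second simulation, with 4,000 trials per setting and an analysis of community proportions, agrees. For child / community correlations 0.3 / 0.5, 0.5 / 0.8 and 0.7 / 0.9, power is 73%, 74%, 73% endline only; 77%, 90%, 97% with baseline anaemia; 65%, 87%, 96% for period by group; and 34%, 31%, 28% for the group term over both surveys.

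**The case against.** A reader might infer that the trial's main anaemia result will be an odds ratio diluted to half its log size, at about 30% power. The documents do not support that. They never say that the surveys are pooled and the interaction left out. They call no test primary, and the primary endpoint is Hb concentration. They do not name anaemia as the logistic outcome; that is inferred because no other model described fits a binary prevalence endpoint. Adjusting for baseline infection also reads more naturally with an endline outcome. If both surveys are fitted together, the plan already commits to testing the period-by-group term, and only its label and place in the report are in question.

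A reader might also infer that only the interaction can measure this endpoint. That is true only of a model holding both surveys. Communities are randomised, so baseline prevalence is equal in expectation and the endline contrast estimates the same between-arm difference in prevalence as the difference in changes. With low correlation the plain interaction is in fact weaker than endline only (58.5% against 76.7%).

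The precision loss can be contested too. The listed malaria and helminth covariates, which the article treats as causes of low Hb, may recover part of it; that model was not simulated. At low correlation, adding baseline anaemia gains only 2.5 to 4 points. The cost-effectiveness analysis is to use unadjusted trial results, so it does not depend on this odds ratio.

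These objections limit the size of the point. They do not remove it: the covariate list is stated, it omits the one baseline value that the endpoint refers to, and the same section handles parasite intensities differently. A separate analysis plan may settle which records enter the model, but the printed list would still need changing.

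**Conclusion.** The point holds as a modest one about efficiency and clarity. With post-intervention data only, the planned group odds ratio is valid. It gives up precision (power about 73–77%, against about 77–98% with baseline anaemia added) and protection against chance imbalance across 20 communities. The gain depends on correlations that the article does not give, and the comparison leaves out the listed covariates, so it is illustrative.

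The shrinkage from about 0.58 to about 0.76 is conditional. It arises only if both surveys are fitted together and a period-averaged group odds ratio is reported. It hardly depends on the assumed correlations, but it does assume equal arms at baseline. The article does not establish that this analysis is planned.

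**What to change.** State that the anaemia effect is the between-arm contrast at the post-intervention survey, from a model that allows for community, and add baseline Hb (or baseline anaemia status) to the listed covariates. Note that the adjusted odds ratio is conditional and should not be compared directly with an unadjusted one.

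If both surveys are to be modelled together, name the period-by-group term as the treatment effect and do not report the period-averaged group odds ratio as the result. Constraining the arms to a common baseline would avoid the power loss of the plain interaction when correlation is low.

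The cost is two or three sentences in the analysis section. No new data are needed, and the change should be fixed before the arms are compared.

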##### Data collection for the cost and cost‐effectiveness analyses

The incremental financial and economic costs of delivering the integrated SMC‐MDA programme in the intervention stage of this study will be estimated from a provider (Government of Ghana and donor) perspective, and compared to the counterfactual of giving SMC drugs alone. Financial cost data (direct expenditure on intervention delivery) and economic costs (donated goods or services, such as time of salaried health workers and schoolteachers) will be collected through review of project records and semi‐structured key informant interviews (KIIs) at district, health facility, CHW and school levels. Detailed costs will be captured for disaggregated cost categories, including SMC and MDA drugs; drug supply chain; school teacher delivery of doses; supervision; training; planning meetings; sensitisation; and supplies. Incremental costs required for the integrated delivery of MDA with SMC above what would be required for SMC delivered alone will be identified. The cost of diagnosis and treatment of moderate and severe anaemia from the health service perspective will be estimated using a combination of primary and secondary data. Cost per outpatient visit and cost per inpatient day (excluding diagnosis and treatment) will be obtained from existing data sources [24, 25]. Costs of diagnostic tests, medicines and provider time for treating cases of moderate and severe anaemia will be captured through KIIs with health staff at facilities providing outpatient and inpatient services in the study area. These parameters will be used to estimate incremental cost savings due to cases of moderate and severe anaemia averted by SMC plus MDA compared to SMC alone.

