The economic analysis will have three parts:a detailed cost analysis of (a) the incremental financial and economic costs of implementing integrated treatment versus SMC alone; (b) modelling costs of delivery at scale; and (c) cost savings from cases of anaemia averted;a budget analysis that compares the net financial costs of delivery at scale minus cost savings from anaemia cases averted against the appropriate Ministry of Health budget to assess if the new intervention is affordable; anda CEA that uses a decision model approach to estimate the ICER of integrated SMC + anti‐helminthic treatment versus SMC alone, in terms of incremental economic costs per incremental measure of effect (DALY averted).

The impact of uncertainty and heterogeneity on results will be explored using deterministic and probabilistic sensitivity analyses to assess the robustness of ICERs to key model parameters (e.g., cost of drugs, effectiveness measures, time taken to deliver MDA in addition to SMC, etc.). The ICER per DALY averted will be compared against context‐appropriate willingness‐to‐pay thresholds [29, 30].

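### The affordability analysis credits salaried provider time as a saving but leaves staff time out of the delivery cost

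*Protocol article*

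**What the plan says.** The section on data collection for the cost and cost-effectiveness analyses sets up two kinds of delivery cost. One is financial: "Financial cost data (direct expenditure on intervention delivery". The other is economic: "economic costs (donated goods or services, such as time of salaried health workers and schoolteachers". Delivery costs in the intervention stage "will be estimated from a provider (Government of Ghana and donor) perspective".

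The same section then turns to treatment costs: "The cost of diagnosis and treatment of moderate and severe anaemia from the health service perspective". These are assembled from unit costs for an outpatient visit and for a day of inpatient care, taken from existing sources, and from interview data: "Costs of diagnostic tests, medicines and provider time for treating cases of moderate and severe anaemia". All of these inputs are said to feed the estimate of savings from anaemia averted. No other version of the saving is described.

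The economic part of the Statistical analysis plan uses the saving in a budget analysis that compares "net financial costs of delivery at scale minus cost savings from anaemia cases averted against the appropriate Ministry of Health budget", in order "to assess if the new intervention is affordable". The cost-effectiveness ratio, in contrast, is explicitly on economic costs.

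**The concern.** A subtraction is meaningful for a budget only if both terms are measured in the same way. Here the delivery term is financial, so by the article's own definition it leaves out the time that salaried staff give to the added deworming. The savings term includes provider time for treating anaemia. If those providers are salaried, their time is an economic cost under the same definition, and freeing it returns no cash to a budget.

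The asymmetry runs in one direction: it favours the intervention. The Discussion links deployment to the approach being predicted cost-effective and affordable at scale, and the budget analysis is the only one described that answers the affordability question. A net figure on mixed bases could be read by the Ministry as a cash requirement when it is not one.

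**Working it through.** The article gives no cost, saving or budget amount, so there is no figure to reproduce. The check sets the definitions against the budget formula.

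**Terms**

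- F: financial cost of delivery at scale (direct expenditure).
- E: salaried staff time spent on the added delivery, an economic cost under the cost-data section and so not in F.
- T: salaried provider time in the anaemia saving.
- C: the rest of the saving (tests, medicines, visit and bed-day unit costs).
- S = C + T: the only saving described.

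**Three net figures**

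1. As written in the Statistical analysis plan: F − S = F − C − T.
2. Both terms financial, treating C as cash: F − C. This exceeds the written figure by T.
3. Both terms economic: (F + E) − (C + T). This exceeds the written figure by E.

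When cases are averted, T is at or above zero. E is at or above zero because deworming adds work. So either way of making the bases agree gives a net cost no lower than the written one.

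**Size**

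Let p = T/S, the share of the saving that is salaried time. The gap between figures 1 and 2 is p × S, and the cash saving is overstated by a factor of 1/(1 − p). The article gives no value of p. The table uses assumed units, F = 100 and S = 40, only to show how the gap behaves; the written figure is 100 − 40 = 60 throughout.

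| p (assumed) | Cash saving, 40 × (1 − p) | Net on a financial basis | Overstatement factor |
|---|---|---|---|
| 0 | 40 | 60 | 1 |
| 0.25 | 30 | 70 | 1.33 |
| 0.5 | 20 | 80 | 2 |
| 0.75 | 10 | 90 | 4 |

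Only at p = 0, when no salaried time is in the saving, do the two figures agree.

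**The case against.** The best reply is that the word net, placed before financial costs, may be meant to put the whole result on a financial basis, savings included. The financial and economic split is also worded for intervention delivery, while treatment costs come later, from a health service perspective, and are not classified. Since the savings inputs are listed separately, a cash-only subset could be tabulated. Part of this stands: the authors may intend a consistent figure, and the data would allow one. But the article describes one saving, states that provider time goes into it, and gives no cash-only version. Followed as written, the plan mixes the bases.

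A reader might infer more than this. Four stronger readings are not supported:

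- **Visit and bed-day unit costs are non-cash.** The article does not give their basis. Only salaried time is non-cash by its own definition.
- **The payer is mismatched.** The government-and-donor perspective is stated for delivery in the intervention stage. Costs at scale are a separate modelling exercise with no stated payer, and the comparator is called the appropriate budget. Extending the perspective to scale is an inference.
- **Children whose anaemia is found only at the survey are costed as treated.** The article does not say so. It refers to a decision model whose parameters a condensed article need not list.
- **The error turns a net cost into an apparent saving.** That depends on assumed prices, and on a severity cut-off that the article does not state.

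The reply is also right that affordability is not among the listed endpoints.

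**Conclusion.** The point holds in a limited form. The budget analysis subtracts a saving that includes provider time from a delivery cost that excludes salaried staff time, so its two terms are on different bases. On this point the bias makes the intervention look more affordable in cash terms. It equals the salaried-time part of the saving, and its size cannot be computed from the article.

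The conclusion rests on two assumptions: that the treating providers are salaried, so that their time falls under the article's definition of economic cost, and that the described saving is the one used in the budget analysis. The overall direction of error in the affordability figure is not claimed. If donor spending did enter the delivery cost at scale, it would overstate the Ministry's burden and push the other way. The primary endpoint and the economic-cost basis of the cost-effectiveness ratio are untouched.

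**What to change.** In the budget analysis, state that both terms are financial:

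- Subtract only tests, medicines and whatever part of the visit and bed-day unit costs is cash, and leave out salaried provider time. State the basis of those unit costs when the sources are chosen.
- On both sides, count only amounts that fall on the Ministry of Health budget used as comparator.
- Keep the full saving, provider time included, for the economic-cost analysis.

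This needs a change of wording and a separate tabulation. Delivery costs are already to be captured by category and the savings inputs are listed separately, so the added work is to identify the cash part of the unit costs and the payer of each item. The small downside is that the net budget figure may become less favourable.

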## DISCUSSION

Malaria‐helminth co‐infection is prevalent among children living in SSA, due to complex interactions of environmental and host factors that support the co‐existence of *Plasmodium* species with parasitic helminths, including STH and *Schistosoma* species [31, 32]. The geographical overlap in the co‐endemicity of helminths and malaria parasites may result in synergistic or antagonistic interactions between helminth and malaria parasites [32, 33, 34]. The additive effects of malaria‐helminth co‐infection on Hb concentration probably contribute substantially to mortality from malaria in children in SSA [1, 35]. Separate vertical implementations of SMC and MDA for helminth control have had limited impact on the prevalence of anaemia [1, 2, 3]. This, therefore, creates an opportunity to exploit the overlap of malaria and helminth to develop and evaluate an integrated approach to achieve effective control of malaria and helminths in endemic settings. This study builds on a previous study that established the safety, tolerability, feasibility and acceptability of the integrated approach. The current trial will address the knowledge gap on the impact and cost‐effectiveness of co‐administration of SMC and anthelminthic drugs on the prevalence of anaemia and malaria‐helminth co‐infection among vulnerable children in a high‐burden country.

The current study was designed and will be implemented in partnership with the Ghana Health Service to facilitate adoption of the integrated SMC‐MDA model and scale‐up if the intervention is found to be effective. In addition, the secondary objectives will inform the deployment of the integrated approach if the intervention is predicted to be cost‐effective and affordable at scale. Findings from this study could have important policy and practice implications for malaria and helminth control programmes across SSA.

